### Data collection

All study visits and interviews are conducted in participant households because of the wide dispersion of households across this rural community and the impracticality of bringing participants to a central location (figure 2). Data collection teams comprising field interviewers (FIs) schedule the study visits, administer the questionnaires and conduct the assessments as described below.

**Figure 2 F2:**
[figure not shown]
MINT Study visits and data collection. Hb, haemoglobin; HH, Household; IYCF, infant and young child feeding; MINT, Maternal Infant Nutrition Trial; VAMS, volumetric absorptive microsampling sample.

#### Enrolment visit

FIs conduct the enrolment visit, after notification of a newly identified pregnancy, to administer informed consent, baseline questionnaires and anthropometry. Questionnaires cover maternal demographic characteristics, socioeconomic status, pregnancy and reproductive history, dietary diversity and household food security (Household Food Insecurity Access Scale developed by the Food and Nutrition Technical Assistance).^27^ Anthropometric measurements include height (portable stadiometer), weight (MicroLife WS50 scale), mid-upper arm circumference (MUAC) (non-stretchable insertion tape), blood pressure and pulse.

#### Ultrasound visit

A special cadre of auxiliary nurse midwives (ANMs) conduct the ultrasound assessment for gestational dating by visiting the participant’s homes (online supplemental material A). ANMs are trained to use a portable machine (SonoSite NanoMaxx) and follow the INTERGROWTH-21st methodology for early and late fetal gestational age assessment, including measurement of crown-rump length and/or biparietal diameter (outer-to-outer), head circumference and femur length.^28 29^

#### Weekly morbidity and supplement compliance visits

Data collectors visit each woman weekly during pregnancy starting at 14 weeks based on last menstrual period and in the postpartum period until 6 months after delivery to provide the supplement, collect data on maternal morbidities and assess supplement compliance.

#### Late pregnancy visit

FIs conduct a late pregnancy visit between 32 and 34 gestational weeks to collect data on maternal anthropometry (same measures as enrolment), maternal morbidities, tobacco/alcohol use, ANC utilisation, delivery planning, diet diversity, household food security and depression (using a version of the Edinburgh Postnatal Depression Scale validated in Nepali).^30^

#### Birth assessment visit

FIs aim to visit each woman within 72 hours of delivery to collect information about the birth and delivery process, early breastfeeding and feeding behaviours, and newborn care practices. Infant weight (g), length (cm), head circumference (cm) and temperature (°F) are measured. Weight is measured with digital scales (Tanita BD-585), length with Shorr-type boards and MUAC with non-stretchable insertion tape. Non-digital measures are taken in triplicate and the median is used for analysis.

#### Postpartum/postnatal monthly visits

After the birth visit, FIs conduct monthly postnatal visits up to 6 months after delivery to administer questionnaires on maternal and infant morbidity, breastfeeding and infant and young child feeding practices, infant care practices, household food security and anthropometric measurements for the infant (weight, length, head circumference, MUAC) and mother (weight, MUAC). Additionally, we will visit as many woman/infant pairs as possible at 12 months after delivery until the administrative end of the study to allow us to assess infant growth at 12 months as a secondary aim in a subsample.

#### Biospecimen substudies

The MINT Study will enrol two substudies for biospecimen collection (online supplemental table 3). First, we will enrol about 120 pregnant women during the first enrolment period from the pregnancy supplementation (n=60) and not groups (n=60). At the enrolment and late pregnancy visits, these women will provide volumetric absorptive microsampling samples, for serum metabolomics analyses collected via finger-stick using Neoteryx kits, haemoglobin measurement, a maternal stool sample stored in nucleic acid buffer solution (DNA Genotek OMR-GUT), and their infants will provide a stool sample at 6 months. Second, we will enrol about 120 pregnant women during the second enrolment period from the pregnancy supplementation (n=60) and not groups (n=60), and these women will provide a haemoglobin measurement at the enrolment and late pregnancy visits, and their infants will provide a stool sample at 3 and 6 months.

#### Dietary intake

FIs will conduct duplicate 24-hour dietary recalls at the late pregnancy and 3 months postpartum visits for a subset of 240 women in the first (n=120) and second (n=120) enrolment periods. The purpose of these data is to assess nutrient intake and determine whether dietary substitution is occurring in the supplement group. Interviewers use the multiple pass method to help the woman recall all the components of her diet from the previous day. A local food list, photo atlas and electronic entry form have been adapted from previous work in Nepal to assist with portion size recall and data entry.^31 32^ Daily nutrient intake will be estimated with local recipes and national food composition tables from India and Nepal.

#### Bayley Scales of Infant and Toddler Development-4 visit

A specialised team with experience and training in developmental assessment in children will visit a subsample of 400 mother/infant pairs to evaluate infant neurodevelopment at 6 months of life.^33 34^ The visit will include the Bayley Scales of Infant and Toddler Development-4 assessment, a standardised evaluation for infants that measures functioning in five areas: cognition, fine motor, gross motor, receptive language and expressive language. At this visit, data collectors will also conduct the WHO six gross motor milestones module.^35^

### Data management

Our FIs administer study questionnaires and record anthropometric measurements via digital tablets with a cellular connection using a customised web-based data management system developed on the Microsoft ASP.NET framework. The local data collectors complete paper forms that are recorded by data entry operators on a weekly basis. On the backend, data are stored in a relational database management system (Microsoft SQL Server). Prior to study launch, the field team tests all forms, and restrictions and checks are programmed to reduce data entry errors. The senior field team member and co-investigators review important variables weekly to monitor data quality issues, such as missingness, heaping, digit preference and outliers. The senior field team member corrects data entry errors and implements retraining of data collectors on specific protocols when necessary.

### Data monitoring

#### Data and Safety Monitoring Board

An independent Data and Safety Monitoring Board (DSMB) is established for the trial to advise the investigators on issues of safety and efficacy. DSMB membership includes four individuals from Nepal, including a paediatrician, obstetrician-gynaecologist, nutritionist and statistician. The DSMB met prior to the start of the study, twice during implementation of the study and will meet at least once more.

#### Serious adverse events

Serious adverse events, as defined under Good Clinical Practice guidelines, include death, a life-threatening reaction to the supplement or other study procedures, hospitalisation for a reason other than routine delivery, significant or persistent disability or impairment, or a congenital anomaly/birth defect. All data collection staff are trained to recognise a range of serious and other adverse events. Serious adverse events are investigated and reported to the DSMB and Institutional Review Boards according to the study research and ethical protocols. Our most senior data collectors conduct verbal autopsies in the case of a maternal or infant death.

### Statistical analysis

#### Primary aim 1

We will undertake an intention-to-treat analysis to examine the effect of supplementation on the first primary outcome of SGA. The analysis will include all live births for whom a birth weight was collected by study data collectors within 72 hours of delivery for the SGA (<10th centile births using the INTERGROWTH-21st standard) outcome. We will assess the balance between the two pregnancy supplementation groups in baseline household-level and individual-level characteristics including maternal age, height, BMI, parity, previous adverse pregnancy outcome, education and socioeconomic status. If imbalanced variables are also associated with the primary outcome (p<0.10), we will use multivariable log binomial regression modelling to adjust for potential confounding. We will compare the proportion of SGA, between those who were supplemented versus not according to their allocation status, using a log binomial regression model to estimate the relative risk and 95% CI with the control group as the referent both unadjusted and adjusted for identified confounders. If the final model does not converge, we will use Poisson regression with robust SE estimation.

#### Primary aim 2

We will undertake an intention-to-treat analysis to examine the effect of supplementation on the second primary outcome of mean LAZ at 6 months. The analysis will include all children whose length was assessed at 6 months of age. We will assess the balance across the four pregnancy and lactation supplementation groups in baseline household-level and individual-level characteristics. If imbalanced variables are also associated with the secondary outcome (p<0.10), we will use multivariable linear regression modelling to adjust for potential confounding. Due to the factorial study design, we will assess the interaction between pregnancy and lactation supplementation on the outcome of mean LAZ, although our sample size is not adequate to detect small interaction effects. We will use a multivariable linear regression model with an interaction term for treatment arms. If the interaction is significant (<0.10), we will report both the main and interaction effects. If not significant, which we anticipate, we will report the marginal treatment effects for supplementation during lactation versus not and during pregnancy versus not. We will compare mean LAZ scores between supplementation groups using a multivariable linear regression model to estimate the risk difference and 95% CI with the control group as the referent both unadjusted and adjusted for identified confounders.

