Despite this context-specific recommendation, the variations in formats, ingredients and nutrient composition have hindered programmatic progress. Further, there is no recommendation for supplementation of women who are breastfeeding, despite high rates of growth faltering in early life in LMICs, where maternal undernutrition is high and exclusive breastfeeding is recommended in the first 6 months of life. Recently, an expert consensus developed specifications for a fortified BEP ‘ready-to-use’ food supplement for pregnant and lactating women in LMICs.^16^ Such a product requires testing in undernourished settings for efficacy in improving birth outcomes and infant growth.

In this paper, we describe the study protocol for the Maternal Infant Nutrition Trial (MINT) at the Nepal Nutrition Intervention Project Sarlahi (NNIPS) research site in Sarlahi District, Nepal. The aim of the MINT Study is to evaluate the efficacy of daily fortified BEP supplementation during pregnancy and lactation on SGA and mean length-for-age z-score (LAZ) in the first 6 months of life. In this rural population, there is a significant burden of undernutrition among mothers and infants and high prevalence of adverse pregnancy outcomes.^17–19^ However, breastfeeding through 6 months of life is high, presenting postpartum supplementation as a plausible mechanism by which to improve infant growth. Our primary hypotheses are that (1) fortified BEP supplementation versus no supplementation during pregnancy will reduce incidence of SGA, and (2) fortified BEP supplementation versus no supplementation during lactation alone or both during pregnancy and lactation will improve infant linear growth in the first 6 months after delivery. Several secondary outcomes will also be examined.

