### Sample size

With a sample size of 1548 woman/infant pairs visited within <72 hours of delivery, we will be able to detect a 17.5% reduction in SGA with 80% power and a 20.2% reduction with 90% power assuming a type 1 error of 5% (two-sided). Since we are assuming no interaction between the marginal effects, this sample size will allow us to detect a difference in infant LAZ at 6 months after delivery of 0.16 z-scores with 80% power and 0.18 z-scores with 90% power. The MINT Study is designed to enrol approximately 1800–2000 women over a period of 20 months (split into two 6-month enrolment periods). This will yield the required sample of 1548 woman/infant pairs visited within 72 hours of delivery, after a reduction of 14% due to fetal death and loss to follow-up in pregnancy.

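### Primary aim 2 lets an interaction test at p<0.10 choose which LAZ effects are reported, and no section names the contrast that decides the aim

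*Protocol article*

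**What the plan says.** Three sections of the protocol article describe the LAZ comparison.

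- **Introduction, hypothesis 2:** "fortified BEP supplementation versus no supplementation during lactation alone or both during pregnancy and lactation will improve infant linear growth".
- **Sample size:** the calculation starts "With a sample size of 1548 woman/infant pairs visited within <72 hours of delivery". The LAZ part is conditional, "Since we are assuming no interaction between the marginal effects", and gives "a difference in infant LAZ at 6 months after delivery of 0.16 z-scores with 80% power and 0.18 z-scores with 90% power". A two-sided 5% type I error is stated once, in the SGA sentence, and is not restated for LAZ.
- **Statistical analysis, Primary aim 2:** a linear model with a treatment-by-treatment interaction term is fitted. Then "If the interaction is significant (<0.10), we will report both the main and interaction effects". If the interaction is not significant, which the authors expect, "we will report the marginal treatment effects for supplementation during lactation versus not and during pregnancy versus not". The control group is the reference. The text concedes that the sample is too small to detect small interactions.

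**The concern.** The reported LAZ effects depend on the result of a test on the same data. One branch uses the term main effects and the other marginal effects, and neither is defined. In a model with an interaction term and 0/1 coding against a control reference, the lactation main effect is the effect in women who were unsupplemented in pregnancy. That is a different quantity from the marginal effect and is estimated from half the data. On that coding, the two branches answer different questions.

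The sections also do not agree on the target. Hypothesis 2 can be read as two cell comparisons (lactation alone v neither, both periods v neither). The sample size is for a marginal effect. The analysis reports two marginal effects in one branch and something else in the other. Both periods v neither is not named as a reported effect in either branch. At stake are the error rate of a primary outcome, and whether a reader can tell in advance which result settles the aim.

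**Working it through.** **Inputs.** N = 1548, two-sided 5%, and detectable differences of 0.16 (80% power) and 0.18 (90%) come from Sample size. The p<0.10 threshold comes from Primary aim 2. Assumed: 1:1 allocation at both randomisations, so 774 v 774 for a marginal effect and 387 per cell. The SD of LAZ is not stated, so it is back-solved. Household clustering and loss between birth and 6 months are left out.

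**1. The plan's own figure.** Detectable difference = (1.960 + z_power) × SD × √(4/1548), with √(4/1548) = 0.0508.
- 0.16 at 80%, allowing for rounding, implies SD 1.088–1.159. 0.18 at 90% implies 1.062–1.123. Both are met by about 1.09–1.12.
- At SD 1.10: 2.802 × 1.10 × 0.0508 = 0.157 and 3.242 × 1.10 × 0.0508 = 0.181. These round to 0.16 and 0.18, so the plan's figures reproduce for a marginal effect.

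**2. Power of the interaction test.** SE = 1.10 × √(4/387) = 0.112. For a true interaction of 0.16, 0.16/0.112 = 1.43, and power at the 0.10 level is about Φ(1.43 − 1.645) = 42%. It is 41% at SD 1.12, and 40% if 0.16 is taken as exactly the 80% point.

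**3. Type I error of the gated lactation test.** In a balanced 2×2, with no true effects, the z-scores for marginal lactation (z_L) and interaction (z_I) are independent standard normal. The reference-coded lactation z is (z_L − z_I)/√2. The gate opens when |z_I| > 1.645. Results from simulating four cell means (4 million replicates, 387 per cell, SD 1.10):

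| Meaning of main effect | Error when gate closed | Error when gate open | Overall |
|---|---|---|---|
| Reference-coded coefficient | 5% | 25% | 0.90 × 5% + 0.10 × 25% = 7.0% |
| Averaged (marginal) effect | 5% | 5% | 5.0% |

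**4. Power with an additive lactation effect of 0.16.** At SD 1.10 the marginal test has 81.6% power. With the gate and reference coding it is 0.90 × 81.6% + 0.10 × 50.7% = 78.5%. If the marginal test is set at exactly 80%, the gated figure is 77%.

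**5. Direct cell comparison, 387 v 387.** Detectable difference = (1.960 + z_power) × SD × √(2/387), with √(2/387) = 0.0719.
- At SD 1.10: 0.22 at 80% and 0.26 at 90%. Over SD 1.09–1.12 the 80% figure is 0.220–0.226. Scaling the stated figure gives 0.16 × √2 = 0.226.
- Power at 0.16 is 51–53%.
- An additive model does not improve precision for both periods v neither. The sum of two marginal effects has variance 2 × 4σ²/1548 = 8σ²/1548, the same as 2σ²/387.

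**The case against.** In factorial usage a main effect is often the effect averaged over the other factor. On that reading the lactation effect is the same in both branches, the gate only adds the interaction, and the error is 5.0%. The rule and its threshold are stated in advance, the weak interaction test is admitted, and an unseen statistical analysis plan could fix the coding. This stands as far as it goes: inflation is conditional on an undefined term. It does not remove the switch, which the article itself states, or supply a deciding contrast.

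Stronger readings that a reader might infer, and why the article does not support them:

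- *The 5% level is lost outright.* It is lost only under reference coding. Allowing a claim on either stratum-specific lactation effect would give 9.4%, but the plan proposes no such claims.
- *The 0.16 is wrong.* It is tied to marginal effects under no interaction, and it reproduces there. That is also the analysis the authors expect to report.
- *Hypothesis 2 means cell contrasts and was left underpowered.* Lactation alone and both periods together make up the lactation-supplemented arm, so the wording can also describe the marginal comparison. Under additivity, lactation alone v neither equals the marginal lactation effect. Both v neither is the sum of two effects: if each were 0.16 (an assumption), the contrast would be 0.32 with about 98% power. The 51–53% applies only to a raw cell comparison at 0.16.
- *Reporting the pregnancy effect on LAZ is out of scope.* The aim in the Introduction covers supplementation in both periods, and reporting both marginal effects is normal for a 2×2 trial. The 9.75% chance of at least one false positive across two marginal tests (1 − 0.95²) arises with no gate at all and is a separate, debatable matter.

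**Conclusion.** The concern holds in a limited form, and the plan should be changed on this point. An interaction test with about 40–42% power for an interaction as large as the design effect chooses which LAZ effects are reported, and nothing says which contrast decides primary aim 2. Under reference coding the cost is about 7.0% type I error instead of 5% for lactation, and about 3 points of power at 0.16 under additivity. Under averaged effects the error is unchanged. The 0.16 and 0.18 are sound for a marginal effect. They do not carry over to a direct cell comparison, where the detectable difference at 80% power is about 0.22–0.23.

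These figures rest on 1:1 allocation, balanced cells, SD 1.09–1.12 and all 1548 pairs being measured at 6 months. Any loss after birth would raise every detectable difference.

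**What to change.** - Delete the p<0.10 switch.
- Name the marginal lactation effect as the primary LAZ contrast, from an additive model with pregnancy arm and height stratum, tested at two-sided 5% and reported whatever the interaction p-value.
- Clarify the comparator in hypothesis 2 to match.
- Always report as secondary: the marginal pregnancy effect on LAZ, the interaction with its 95% CI, and the cell contrasts (lactation alone v neither, both periods v neither), with their detectable difference of about 0.22–0.23 before loss to 6 months.

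This holds the lactation test at 5.0% and keeps the stated 0.16 valid. It needs wording and a little more reporting, but no more participants or data. The trial is unblinded and 1944 women were enrolled by August 2023, so the change should be dated and made before LAZ is examined by arm.

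The price is that a real interaction would be averaged over. For example, if lactation alone did nothing and the interaction were 0.16, the marginal lactation test would reject about 30% of the time (SD 1.10), against 20% with the gate under reference coding. The gate limits that problem without removing it. Showing the cell estimates beside the primary result lets the reader see it.

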### Patient and public involvement

We conducted two formative studies to assess compliance with and acceptability of various formulations of BEP supplements. Our field leadership team also engaged several local stakeholders prior to the start of the study, including municipality mayors, health coordinators and health facility in charge in the study area. After completion of the study, the team will conduct similar meetings to disseminate the results.

### Ancillary care

The MINT Study provides iron–folic acid tablets and albendazole to women who report that they have not received these from the health facility during their ANC visits. Women with low haemoglobin (<110 g/L) are referred to a health facility. Women with suspected fetal abnormality detected during the ultrasound gestational age dating visit are referred for clinical examination.

### Confidentiality

Study investigators and staff treat all data as confidential, and participants are informed that their information will be protected. All data collection forms are kept in secure locations with access limited to relevant study staff. All electronic databases are stored on encrypted, password-protected servers, and data transfer uses secure encrypted transfer protocols. Access to identifying information is restricted to the principal investigator and few key co-investigators and staff. Only anonymised datasets are shared beyond the study team.

### Dissemination plan

The study team will disseminate MINT findings to the Sarlahi District Public Health Office, Sarlahi District Project Advisory Committee, Ministry of Health and Population, Nepal, Central Project Advisory Committee, and to various local organisations, including UNICEF-Nepal and UNICEF South Asian Regional Office, US Agency for International Development and other stakeholders in Nepal with interests in nutrition during pregnancy and lactation. We will share anonymised data with the Ki data repository and researchers involved in the BEP Harmonization Initiative organised and funded by the Bill & Melinda Gates Foundation for the purpose of meta-analyses using data from similar trials conducted around the world. The study team will also present results at international workshops and conferences with relevant researchers and programme or policy stakeholders. Members of the study team will publish results of primary and secondary analyses in peer-reviewed academic journals.

